## Introduction

Neoadjuvant chemoradiotherapy (nCRT) followed by total mesorectal excision (TME) has been the standard treatment for locally advanced rectal cancer, significantly reducing local recurrence rates [1–4], particularly in cases with threatened mesorectal fascia (MRF) or a positive circumferential resection margin (CRM) [5,6]. However, despite its oncologic benefits, nCRT is associated with considerable morbidity, including bowel dysfunction, fecal incontinence, and sexual dysfunction, which can severely impact patients’ quality of life (QoL) [2,3,7]. Additionally, with advancements in rectal cancer surgery, the necessity of nCRT for all locally advanced rectal cancer cases has been increasingly debated.

Several studies, including OCUM, MERCURY, and QuickSilver, have investigated more selective approaches to nCRT to minimize overtreatment while maintaining oncologic safety [8–10]. These studies have demonstrated that MRI-predicted negative CRM strongly indicates favorable oncologic outcomes, allowing for primary surgery without nCRT in appropriately selected patients. The OCUM trial, in particular, showed that patients with magnetic resonance imaging (MRI)-negative CRM undergoing upfront TME had an acceptably low local recurrence rate (<10%) at five years [8]. The MERCURY trial further validated MRI as a reliable tool for preoperative risk stratification, demonstrating a high accuracy in predicting negative CRM and a low risk of local recurrence in MRI-negative patients [9]. Despite these promising results, the optimal selection criteria for omitting nCRT remain a subject of ongoing research.

Current European guidelines, including those from the European Society for Medical Oncology (ESMO), advocate a risk-adapted approach to nCRT. According to ESMO, patients with cT3a/b rectal tumors located above the levator muscles, without CRM involvement or extramural vascular invasion, are considered to have a low risk of local recurrence and may be candidates for upfront surgery without nCRT [11]. This contrasts with North American guidelines, which still recommend routine nCRT for stage II and III rectal cancers [12]. However, given that modern surgical techniques have significantly reduced the risk of CRM positivity and local recurrence, a more selective approach to nCRT may be warranted.

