#### Secondary outcome measures.

5-year DFS: The proportion of patients who remain free of disease recurrence (local or distant) five years after surgical intervention.3- and 5-year Overall Survival: The proportion of patients alive at 3- and 5-years post-treatment, regardless of disease status.3- and 5-year Local Recurrence Rate: The percentage of patients experiencing tumor recurrence at the primary site (anastomosis or pelvis) within 3 and 5 years.1-, 3- and 5- year Colorectal Cancer Specific Quality of Life: Patient-reported outcomes assessed using the New Cleveland Clinic Colorectal Cancer Quality of Life Questionnaire [14].1-, 3- and 5- year Bowel Dysfunction Related Quality of Life: Patient-reported outcomes assessed using the low-anterior resection syndrome (LARS) score [15].

Fig 1 represents the timeline of anticipated recruitment and outcome measures.

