### Statistical methods

During the study, missing data analyses and data quality assessments will be actively conducted, and measures to prevent data loss and enhance data quality will be implemented as appropriate. All statistical analyses will be conducted by experts from the TSCRS Biostatistics and Bioinformatics Analysis Unit using SPSS (SPSS Inc, Chicago, IL) software packages.

Multivariable regression analyses will be conducted to evaluate the effect of treatment strategy (direct TME vs. nCRT followed by TME) on the primary and secondary outcomes. The following covariates will be included in the models based on clinical relevance and literature review: age, sex, clinical T stage (cT2 vs. cT3), clinical N stage (N0 vs. N+), tumor differentiation, regimens of neoadjuvant treatment (long-course CRT, short-course RT, TNT with long or short-course RT), interval between neoadjuvant RT/CT and surgery, comorbidities (e.g., Charlson Comorbidity Index), performance status, postoperative complications (Clavien-Dindo), tumor histology, pathologic TME quality (pathologic completeness of the mesorectum), and center effect (as a random effect if appropriate).

For time-to-event outcomes such as disease-free survival (DFS) and overall survival (OS), Cox proportional hazards regression models will be used to estimate hazard ratios and 95% confidence intervals. The proportional hazards assumption will be tested using Schoenfeld residuals.

To address potential selection bias due to the non-randomized design, propensity score methods will be applied. Specifically, propensity scores for receipt of nCRT (vs. direct TME) will be estimated using logistic regression including the aforementioned covariates. The primary analysis will adjust for the propensity score as a covariate in the Cox model. Sensitivity analyses will be conducted using propensity score matching (1:1 nearest neighbor matching without replacement) and inverse probability of treatment weighting (IPTW) to ensure the robustness of results.

Patients lacking the main data specified in the inclusion and exclusion criteria, demographic data, or follow-up data related to the primary endpoint will be completely excluded from the study. Patients with missing data from other variables or secondary endpoints will only be excluded from those specific analyses, and secondary endpoints will be evaluated using data from patients with complete datasets.

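### The fixed covariate list is too long for local recurrence: at most about 40 events for 14 to 22 parameters, and the propensity score as specified cannot replace it

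*Protocol article*

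**What the plan says.** Statistical methods opens with "Multivariable regression analyses will be conducted to evaluate the effect of treatment strategy" and gives the scope as "direct TME vs. nCRT followed by TME) on the primary and secondary outcomes". It then fixes the adjustment set: "The following covariates will be included in the models based on clinical relevance and literature review". The list names 12 covariates: age, sex, clinical T stage, clinical N stage, differentiation, neoadjuvant regimen, interval to surgery, comorbidity, performance status, postoperative complications, histology and TME quality. Centre is added with the wording "center effect (as a random effect if appropriate". Several entries have more than two levels, for example "regimens of neoadjuvant treatment (long-course CRT, short-course RT, TNT with long or short-course RT" and "postoperative complications (Clavien-Dindo), tumor histology, pathologic TME quality (pathologic completeness of the mesorectum". No shorter list, penalisation or event limit is given for rare outcomes.

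Secondary outcome measures defines local recurrence as "The percentage of patients experiencing tumor recurrence at the primary site (anastomosis or pelvis) within 3 and 5 years". The Introduction gives the only figure for its frequency: patients with a clear MRI margin who had upfront TME in a cited study "had an acceptably low local recurrence rate (<10%) at five years".

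Propensity methods appear later in Statistical methods. The score is to be estimated by logistic regression on the same covariates. It enters the Cox model of the primary analysis as a covariate, with matching and weighting as sensitivity analyses. Nothing says that it replaces the list for secondary outcomes.

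**The concern.** A regression with as many parameters as events, or nearly so, is poorly supported. Some covariate levels will contain no events, and their coefficients then run off to infinity. The other coefficients, treatment included, lose precision. Local recurrence is the outcome that the Introduction credits nCRT with reducing. The low-risk eligibility definition is built on it, and it is one of the discontinuation criteria. An avoidably noisy estimate there weakens the evidence on whether nCRT can safely be omitted.

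**Working it through.** **Sample size.** Sample size and recruitment gives 396 evaluable and 436 enrolled patients. The 396 is reproduced by a non-inferiority comparison of two proportions of 80%, taking a 10-point margin and one-sided alpha of 0.05 (both inferred; the article states neither): (1.645 + 0.842)² × 2 × 0.8 × 0.2 / 0.10² = 197.9, so 198 per group. Then 198 × 1.10 = 217.8, so 218 per group and 436 in all.

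**Events.** Events = N × rate. The 10% bound is from the Introduction and is applied here to both groups. The 4 to 8% range is an assumption inside it.
- 396 × 0.04 = 15.8
- 396 × 0.06 = 23.8
- 396 × 0.08 = 31.7
- 396 × 0.10 = 39.6

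**Parameters, centre excluded.** The leanest coding is treatment (1), eleven covariates with one parameter each (11) and regimen in three levels (2), which makes 14. Ordinary categorical coding gives about 18 to 22. The article does not state the coding.

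**Events per parameter.**

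| Parameters | 4% | 6% | 8% | 10% |
|---|---|---|---|---|
| 14 | 1.1 | 1.7 | 2.3 | 2.8 |
| 18 | 0.9 | 1.3 | 1.8 | 2.2 |
| 22 | 0.7 | 1.1 | 1.4 | 1.8 |

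No cell reaches 3. Using all 436 patients changes little: 4 to 8% gives 17 to 35 events. For comparison, 80% DFS gives 396 × 0.20 = 79 events, or 3.6 to 5.7 per parameter.

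**Simulated fits.** Percentage of data sets with at least one diverging coefficient, by number of events (logistic runs: by rates of 4, 6, 8 and 10%). Covariate prevalences are assumed throughout.

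| Model | Parameters | 16 | 24 | 32 | 40 |
|---|---|---|---|---|---|
| Cox, 700 replicates | 18 | 37 | 15 | 4 | not run |
| Cox, 250 replicates | 18 | 25 | 6 | 2 | not run |
| Cox | 17 | 93 | 59 | 37 | 27 |
| Logistic, 1000 replicates | 14 | 56 | 26 | 11 | 5 |
| Logistic, 1000 replicates | 21 | 97 | 85 | 68 | 52 |

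The spread shows how far the answer depends on coding and on the assumed prevalences. The treatment coefficient itself diverged in 0% of the 250-replicate Cox fits, under 1% of the 17-parameter Cox fits and at most 2.5% of the logistic fits.

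**Precision of the treatment effect.** In the 700-replicate Cox runs, the SD of the treatment log-HR under the full list against propensity-only adjustment was:
- 16 events: 0.797 against 0.627, variance ratio (0.797/0.627)² = 1.62
- 24 events: 0.525 against 0.475, ratio 1.22
- 32 events: 0.457 against 0.418, ratio 1.20

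Type I error was 6 to 7% against 4 to 5%. The 17-parameter Cox check gave variance ratios of about 1.1 to 1.25 against a baseline propensity score.

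**The score as specified.** Regimen and interval to surgery exist only in the nCRT group. If direct-TME patients are coded as having no regimen, regimen identifies treatment perfectly. Adding three regimen indicators gave fitted scores of at least 0.99999 for nCRT and at most 0.0000001 for direct TME. As a covariate, such a score duplicates treatment; as weights, all near 1, it balances nothing.

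**The case against.** **The harm is modest.** A reader might infer that the local recurrence analysis will collapse, or give false positives. The checks do not support that. The diverging coefficients sit mostly in sparse covariate levels, the treatment estimate rarely diverges, and type I error moves little. The variance ratio of 1.6 belongs to 16 events only, where over a third of those fits had a non-finite coefficient, so it should be read with caution. This objection stands and limits the point to frequent non-finite nuisance coefficients and a modest loss of precision.

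**The event count is assumed.** This also stands. A reader might take 16 to 32 as the trial's expected number, but the article supports only a ceiling near 40, and that by carrying a cited upfront-TME figure over to both groups. The conclusion does not depend on the assumption, since the ceiling itself gives fewer than 3 events per parameter. Complete-case handling of secondary endpoints, and a single date of August 2030 for the end of both recruitment and study, could lower the usable count further.

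**The plan already has a propensity score.** The text does not expressly confine propensity methods to DFS, so the full list may not be the only local recurrence analysis. But a reader who infers that the existing score solves the problem would be mistaken: as specified it separates the two groups perfectly.

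**This belongs in the analysis plan.** Trimming a model for one sparse endpoint is often left there, and that document is not shown. Here, however, the article states a rule that covers secondary outcomes without exception. The point concerns that stated rule, not a missing detail.

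**Not every secondary outcome is affected.** Correct. The quality-of-life and LARS scores are not event counts and lie outside this point. The article gives no event figure for overall survival.

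**Conclusion.** The point holds in a limited form. As written, the full list goes into the local recurrence model with about 0.7 to 2.8 events per parameter. This rests on 396 evaluable patients, a rate of 4% up to the article's 10% bound, and 14 to 22 parameters. Some coefficients for sparse levels will frequently be non-finite; how often depends on coding and rate. The treatment effect remains estimable, with a variance about 1.1 to 1.6 times what propensity-only adjustment would give. Its confidence interval on the log scale is thus about 5% (√1.1 = 1.05) to 26% (√1.6 = 1.26) wider than it need be.

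The loss is avoidable, but the remedy will not make local recurrence precise. Even a crude comparison of equal groups has a 95% interval spanning a factor of exp(1.96 × √(4/16)) = 2.7 either side at 16 events and exp(1.96 × √(4/32)) = 2.0 at 32. The point is worth correcting before data exist. It does not threaten the primary analysis on this ground.

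**What to change.** For local recurrence, and for any other event-type secondary endpoint with too few events for the list, drop the full-covariate model. Estimate the treatment effect with a propensity score alone, either as weights or as a single covariate, and state which.

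Build that score from pre-treatment covariates only: age, sex, clinical T stage, clinical N stage, differentiation, histology, comorbidity and performance status. Leave out neoadjuvant regimen, interval to surgery, postoperative complications and TME quality. Merely shortening the outcome model to the baseline covariates is not enough: with about 10 parameters, 16 to 32 events still give only 16/10 = 1.6 to 32/10 = 3.2 per parameter.

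Report adjusted 3- and 5-year local recurrence rates per group, with the difference and its 95% CI. This also matches the definition of the endpoint as a percentage.

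The cost is analysis wording. What is lost is a table of prognostic-factor coefficients for local recurrence, which would be unreliable anyway. The analysis of the quality-of-life and LARS scores need not change on this account.

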### Trial design

The CANO trial is a prospective, non-randomized, observational, cohort study. Patients undergoing TME will be included in the study, with a comparative analysis between those receiving neoadjuvant chemoradiotherapy and those who do not. The design precludes any possibility of cross-over between the groups.

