#### Inclusion criteria.

Pathologically confirmed rectal cancerRectal cancer within 6–12 cm from anal verge confirmed by sigmoidoscopy or located between the anorectal junction and peritoneal reflection identified by MRIClinically staged with pelvic MRI and thoracoabdominal computed tomography (CT)Local clinical stages cT2N+, cT3N0 and cT3N+Patients without MRF involvement assessed by MRI (≤1 mm)Patients without pathological LPLN (short axis ≥7 mm) on MRIPatients without EMVI on MRIPatients who underwent open, laparoscopic or robotic TME

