### Interventions

The standard of care for the treatment of locally advanced rectal cancer is TME. In patients with cT2N+, cT3N0, and cT3N+ mid-rectal tumors, the administration of nCRT, as well as the direct TME, are both considered guideline-concordant standard treatment approaches and are widely practiced [11,12]. In this study, data from patients undergoing TME as part of routine medical care will be collected prospectively. No additional interventions, treatments and follow-up protocols outside of standard care will be implemented. At the end of the study, patients will be categorized into two groups based on whether they received nCRT and the two groups will be compared in terms of primary and secondary endpoints. No treatment or monitoring protocols differing from routine practice will be proposed for patients or surgeons in the study. The natural prognosis of the treatment arms will be observed.

All the patients undergoing TME described as a precise dissection of the rectum along with the surrounding mesorectal tissue and all pararectal lymph nodes are eligible for the study [13].

**Direct TME Group:** Patients who undergo direct TME without neoadjuvant treatment.

**nCRT Group:** Patients who receive nCRT prior to TME.

Neoadjuvan CRT treatments include all conventional chemoradiotherapy regimens or total neoadjuvant chemoradiotherapy regimens (standard short or long course radiation and/or any standard chemotherapy regimen) described in European and American guidelines [11,12]. The details of radiotherapy and chemotherapy treatments will be recorded, including dosage, frequency, duration, complications, completion status, and the waiting period between treatments. Routine follow-up information for all patients including morbidity, radiologic assessments, recurrence, mortality be recorded in the database for the first five years post-surgery. Patient-reported quality of life scales will be recorded at baseline (prior to the initiation of treatment) and subsequently at 1, 3, and 5 years.

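### T stage is adjusted for only as cT2 versus cT3, so cT3 substage, a factor in the guideline the protocol cites, is a likely residual confounder in every planned analysis

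*Protocol article*

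**What the plan says.** The Trial design section states that "The CANO trial is a prospective, non-randomized, observational, cohort study". Treatment is therefore chosen in routine care, and the comparison depends on covariate adjustment.

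The Statistical methods section lists the covariates together with their coding: "clinical T stage (cT2 vs. cT3), clinical N stage (N0 vs. N+), tumor differentiation", followed by patient, treatment, surgical and centre variables. No item on the list carries cT3 substage, depth of extramural spread or distance to the mesorectal fascia. The propensity score is to be "estimated using logistic regression including the aforementioned covariates". It is then used as follows: "The primary analysis will adjust for the propensity score as a covariate in the Cox model". Matching and IPTW on the same score are the sensitivity analyses.

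The Introduction describes the European guideline as identifying "patients with cT3a/b rectal tumors located above the levator muscles, without CRM involvement or extramural vascular invasion" as low risk, and says that these patients "may be candidates for upfront surgery without nCRT". It contrasts this with North American guidance, which it describes as still recommending routine nCRT for stage II and III disease.

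The Inclusion criteria give the stages as "Local clinical stages cT2N+, cT3N0 and cT3N" (a plus sign follows in the text), with no limit on cT3 substage. They do exclude MRF involvement and EMVI, and they restrict tumour location.

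**The concern.** A propensity score removes confounding only by the variables in it, in the form in which they are entered. Where a factor influences both the choice of nCRT and the outcome, merging its levels leaves confounding within the merged level. Here all cT3 tumours form one level, although the guideline that the protocol cites separates cT3a/b from deeper cT3 when identifying candidates for surgery alone.

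Direction matters because the Discussion describes the aim as showing non-inferior 3-year DFS for upfront TME. If deeper tumours are steered to nCRT and recur more often, the nCRT group carries a heavier case mix and direct TME looks better than it is. That favours the conclusion the study hopes to reach. The two sensitivity analyses would not expose the problem, because they use the same score.

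**Working it through.** **1. Which guideline conditions are left open**

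| Condition cited in the Introduction | Handled by eligibility? | In the covariate list? |
|---|---|---|
| CRM not involved | Yes, MRF involvement excluded | Not needed as a yes/no factor |
| No EMVI | Yes, excluded | Not needed |
| Above the levators | Location restricted to the mid-rectum | Not listed |
| cT3a/b | No, every cT3 admitted | Only as cT2 vs cT3 |

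Substage is the one named condition that is neither restricted nor adjusted for. This holds whatever the numbers below.

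**2. The protocol's own sample size**

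The Sample size and recruitment section gives 80% 3-year DFS in both groups, α = 0.05, 80% power and 396 patients at 1:1. It states neither a margin nor sidedness. With a 10-point non-inferiority margin and a one-sided 5% test:

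n per group = (1.645 + 0.842)² × 2 × 0.80 × 0.20 / 0.10² = 197.8, so 198, and 396 in total.

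This reproduces the stated figure. One-sided 2.5% would give 252 per group, or 504. A two-sided superiority test of 80% vs 90% gives 398, which is close, but it conflicts with the stated equal rates. The margin and sidedness are therefore inferred. The only 10% difference in the protocol is a stopping threshold.

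**3. Illustrative size of the bias**

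The documents give neither the cT3c/d share in each group nor its prognostic effect, so both are assumed.

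Setup: no true treatment effect; proportional hazards for depth with ratio g; mean 3-year DFS over the two groups fixed at the protocol's 80%. Let S be 3-year DFS in shallower tumours, so that deeper tumours have S^g. A group with deep share p has DFS = p·S^g + (1 − p)·S.

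Worked case, shares 40% (nCRT) vs 10% (direct TME), g = 2.0:
- Mean share 0.25: 0.25·S² + 0.75·S = 0.80 gives S = 0.8345 and S² = 0.6964.
- nCRT: 0.4 × 0.6964 + 0.6 × 0.8345 = 0.779.
- Direct TME: 0.1 × 0.6964 + 0.9 × 0.8345 = 0.821.
- Apparent difference: 4.1 points in favour of direct TME.

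**4. Effect on a non-inferiority conclusion**

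SE = √(2 × 0.16 / 198) = 0.0402. With direct TME truly 10 points worse, the chance of declaring non-inferiority is Φ(bias / 0.0402 − 1.645). For the worked case: Φ(0.0414 / 0.0402 − 1.645) = Φ(−0.61) = 0.27.

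| cT3c/d share, nCRT vs direct TME | Depth HR | Bias (DFS points) | Apparent HR, direct TME / nCRT | False non-inferiority |
|---|---|---|---|---|
| Equal shares, or depth HR 1.0 | – | 0 | 1.00 | 5% |
| 20% vs 10% | 1.5 | 0.8 | 0.96 | 7% |
| 20% vs 10% | 2.0 | 1.5 | 0.92 | 10% |
| 40% vs 10% | 1.5 | 2.3 | 0.88 | 14% |
| 40% vs 10% | 2.0 | 4.1 | 0.79 | 27% |

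Three simplifications apply. The bias is calculated with no treatment effect and then carried to the margin. No credit is given for N stage, differentiation, histology or centre, which may absorb part of it. The SE uses 80% in both groups; with 80% vs 70% it is √(0.37 / 198) = 0.0432, and the range becomes about 7% to 25%.

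**The case against.** The strongest reply is that the protocol does not say that substage drives treatment choice. The Introduction reports one guideline, under which several joint conditions make a patient a possible candidate. Where the protocol describes practice, in its Discussion, it speaks of upfront TME for T2-3 node-positive tumours without MRF involvement and does not mention substage. Choice may instead follow whichever guideline a centre uses, and a centre effect is on the covariate list. Excluding MRF involvement and EMVI may also narrow any imbalance in depth. This stands: confounding by substage is inferred and its size is unknown. It does not remove the point, because a named and measurable guideline factor still goes unadjusted. The Limitations section concedes residual confounding only in general terms.

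A reader might infer three stronger things, none of which the documents support:
- **A measured bias.** The documents contain no substage shares, no prognosis by substage and no stated margin.
- **That substage is not collected.** The full variable list is in a supplementary file (S2) that is not shown and may hold it. The coding in the models is nevertheless stated, so it is not a detail left to a separate analysis plan.
- **That the protocol contradicts itself on the guidelines.** The Interventions section says that "the administration of nCRT, as well as the direct TME, are both considered guideline-concordant standard treatment approaches" for cT2N+, cT3N0 and cT3N+ mid-rectal tumours. That sits uneasily with the Introduction, but the Introduction does not say that direct TME is discordant for deeper cT3, and settling the matter would need the guidelines themselves.

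**Conclusion.** The point holds as a likely residual confounder that the plan could adjust for and does not. The coding is certain and is common to the primary Cox model, matching and IPTW. The direction, towards direct TME, rests on two assumptions: that deeper tumours more often receive nCRT, and that they have worse DFS. The illustrative 0.8 to 4.1 points, and the rise in false non-inferiority from 5% to about 7–27%, further depend on the assumed shares and hazard ratios and on the inferred margin and test. The bias could be zero. It is a change that should be made, with medium confidence, because the remedy is cheap and substage may not be recoverable later from reports that omit it.

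**What to change.** - Ensure that cT3 substage (a/b vs c/d) or depth in mm from the baseline staging MRI is recorded, if the database does not already hold it.
- In the Statistical methods section, replace the two-level T stage with cT2 / cT3a-b / cT3c-d, or with depth, in both the propensity and outcome models, and report its balance between groups.
- Keep patients with missing substage in the primary model, for example by multiple imputation. As written, patients with missing data on other variables are excluded from the analyses that use them, so a partly missing substage would cost patients.
- Optionally, clarify how the Interventions wording for all cT3 tumours fits the Introduction's description of the guidelines. No view is taken here on which clinical rule is right.

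Cost: at most one baseline field, taken from an MRI that every patient must have, and one further model parameter. The sample size of 396 does not change. The article gives recruitment as not yet started, so the field could be in place from the first patient. The downside is that some reports may lack substage, and readings may vary between centres without central imaging review, so adjustment will remove only the confounding carried by substage as recorded.

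### The fixed covariate list describes baseline tumour extent only as cT2/cT3 and N0/N+, leaving out MRI distance to the mesorectal fascia and pooling cN1 with cN2, so confounding by these may remain

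*Protocol article*

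**What the plan says.** All references are to the protocol article.

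- **Trial design:** "The CANO trial is a prospective, non-randomized, observational, cohort study". The Interventions section adds that treatment is whatever routine care delivers.
- **Statistical methods, outcome models:** the list is explicit. It opens "The following covariates will be included in the models based on clinical relevance and literature review: age, sex, clinical T stage (cT2 vs. cT3") and continues "clinical N stage (N0 vs. N+), tumor differentiation". No other item describes baseline tumour extent.
- **Statistical methods, propensity score:** the same list is reused: "propensity scores for receipt of nCRT (vs. direct TME) will be estimated using logistic regression including the aforementioned covariates".
- **Statistical methods, primary analysis:** "The primary analysis will adjust for the propensity score as a covariate in the Cox model". Matching and IPTW are the sensitivity analyses.
- **Inclusion criteria:** the fascia appears only as a cut-off, "Patients without MRF involvement assessed by MRI (≤1 mm"). The eligible stages are cT2 node-positive and cT3 with or without nodes, with no limit on the number of mesorectal nodes. EMVI and lateral nodes of 7 mm or more are excluded.
- **Introduction:** the reduction in local recurrence with nCRT is described as holding "particularly in cases with threatened mesorectal fascia (MRF) or a positive circumferential resection margin (CRM"), and an MRI-predicted clear margin is given as the basis for omitting nCRT.
- **Limitations:** residual confounding is conceded in general terms, without naming a variable.

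**The concern.** In a non-randomised comparison, the adjustment should contain the pre-treatment features that influence both the choice of treatment and the outcome. The staging MRI is required for eligibility and is read before treatment is chosen. The Introduction treats margin status on that MRI as central to whether nCRT is needed. Yet within the eligible population the models cannot tell a tumour just over 1 mm from the fascia from one many millimetres away, nor one suspicious node from several.

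If clinicians send patients with closer margins or more nodes to nCRT, and those features worsen prognosis, the direct-TME group has the better prognosis at equal propensity score. The adjusted comparison would then lean towards calling omission of nCRT safe. That is the unsafe error for the non-inferiority aim in the Discussion section. It is equally unsafe for the hypotheses under Main question, where the alternative is that direct TME is worse.

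The primary analysis, matching and IPTW all use the same score, so agreement between them would not reveal the gap.

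**Working it through.** **Step 1. Is the gap in the text?** Set eligibility against the covariate list.

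| Feature on staging MRI | Range left by eligibility | Term in the models |
|---|---|---|
| Distance to fascia | every value above 1 mm | none |
| Mesorectal nodes | N0 and any N+ | N0 vs N+ |
| EMVI, lateral nodes ≥7 mm, cT4 | excluded | none needed |

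Restriction deals with the last row but not the first two. Because the list and its categories are stated, this is a choice the protocol has made, not detail left to an analysis plan.

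**Step 2. The plan's own figure, for scale.** The Sample size section gives 80% DFS in both groups, α = 0.05, 80% power and 396 patients, but no margin and no sidedness. A non-inferiority calculation with a 10-point margin and one-sided 0.05 reproduces it:

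n per group = (1.645 + 0.842)² × 2 × 0.80 × 0.20 / 0.10² ≈ 198, so 396 in total; 396 × 1.10 ≈ 436.

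The margin and sidedness are therefore inferred. One-sided 0.025 with the same margin would need 504.

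**Step 3. Illustrative bias from one omitted binary factor.** The document gives no prevalences and no hazard ratios (HRs), so all inputs here are assumed. Let S be 3-year DFS without the factor, HR its effect on DFS, and q1 and q0 its prevalence in the nCRT and direct-TME groups. With no true treatment effect:

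apparent advantage of direct TME = (q1 − q0) × (S − S^HR)

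With S = 0.82:

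- q1 = 25%, q0 = 10%, HR 1.5: 0.15 × (0.820 − 0.743) = 1.2 points
- q1 = 25%, q0 = 10%, HR 2.0: 0.15 × (0.820 − 0.672) = 2.2 points
- q1 = 35%, q0 = 10%, HR 2.0: 0.25 × (0.820 − 0.672) = 3.7 points

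A second set of assumptions fixes DFS at 80% in the nCRT group, with q0 = 20%, q1 = 30–50% and HR 1.5–2.5. It gives 0.8 to 4.7 points (apparent HR 0.96 to 0.75). Reversing the imbalance (q1 = 20%, q0 = 40%) gives −1.6 to −3.9 points, against direct TME.

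**Step 4. What such a shift would do.** Take a true deficit of exactly 10 points, the inferred margin, and 198 per group:

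SE = √[(0.80 × 0.20 + 0.70 × 0.30)/198] = 0.0432

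false acceptance = Φ(shift/SE − 1.645)

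- no shift: 5%
- 1 point: Φ(−1.41) = 7.9%
- 3 points: Φ(−0.95) = 17.1%
- 3.7 points: Φ(−0.79) ≈ 21%

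The second set of assumptions gives about 7% to 30%. This formula tests a difference in proportions, whereas the planned primary analysis is a Cox hazard ratio, so these percentages show scale only.

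**Step 5. Would adding the terms work as the list stands?** Not in the propensity score. The list includes neoadjuvant regimen and the interval from neoadjuvant treatment to surgery. Both exist only in the nCRT group, so a score built on them nearly determines treatment, and balance on any other variable cannot then be assessed. Postoperative complications and TME quality arise after treatment and do not belong in a propensity score either.

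**The case against.** The case against is substantial, and most of it stands as a limit on size and certainty.

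- **Direction.** A reader might infer that the omission demonstrably biases the trial towards direct TME. The document reports no data on nCRT use by margin distance or node count, and the reversed imbalance in the working changes the sign. Only a conditional statement is supported.
- **Prognostic gradient.** The Introduction speaks of threatened or positive margins and of MRI-negative margins, which is a binary status, and eligibility already removes involvement at 1 mm or less. Nothing in the document says that distance beyond 1 mm, or cN2 against cN1, predicts DFS. The gradient is a reasonable extension, not a statement of the protocol.
- **Size.** A reader might take 1 to 4 points as the residual bias. Those figures use raw prevalence gaps. cT, cN and centre are in the models and may absorb part of the imbalance. The calculation uses a generic factor, and no inputs specific to nodal burden are available. The false-acceptance figures also rest on an inferred margin.
- **Feasibility.** Eligibility needs only a classification at 1 mm. Data collection and management mentions clinical stages, not millimetres, and the variable list (S2 File) is not shown. It cannot be assumed that distance is recorded.
- **Acknowledgement.** Limitations already concedes residual confounding. It names neither variable, however, and this part of the confounding could be reduced with pre-treatment information.

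None of this alters the fact that the stated list leaves out one pre-treatment MRI feature and coarsens another.

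**Conclusion.** The point holds in a limited form. The covariate list, as fixed, cannot adjust for distance to the fascia above 1 mm or for differences in nodal burden among node-positive patients, and every planned propensity analysis shares that gap. The confounding would favour direct TME if closer margins or more nodes lead to nCRT and carry worse DFS. Both conditions are plausible, and neither is shown in the document.

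The size is unknown. The illustrations only show that an effect that is material against a 10-point margin is possible under moderate assumptions. They do not estimate the bias, and they do not support a claim that the trial will wrongly find direct TME safe.

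The change is worth making now because the article states that recruitment had not started. Millimetre distances would be harder to recover later from centres without central imaging review.

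**What to change.** In Statistical methods:

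1. **Limit the propensity model to pre-treatment variables.** Remove nCRT regimen, radiotherapy-to-surgery interval, postoperative complications and TME quality. Without this step the remaining changes achieve little.
2. **Code cN as N0/N1/N2** in the propensity model.
3. **Add the shortest baseline MRI distance to the mesorectal fascia**, in millimetres. If the database holds only yes/no, add a numeric field before the first patient is entered.
4. **Report balance** on both variables after matching and after weighting.
5. **Add the terms to the outcome model only as events allow.** At 80% DFS, 396 patients give about 0.20 × 396 ≈ 79 events by 3 years, against 13 covariate items already listed, several with more than two levels.

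**Cost.** The sample size of 396 (436 with dropout) does not change. One data field may be needed. Distance will carry between-centre measurement error, since Limitations notes variable MRI reading without central review. It will also have some missing values; because patients with other missing variables are dropped from the analyses concerned, an incomplete field would shrink the primary analysis, so it should be required at baseline entry. The propensity model gains a few parameters.
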